**Other measures**					
Depression	Beck Depression Inventory (BDI) [20]	X	X		
Psychological distress	SCL90 [21]	X			
Cognitions regarding fatigue	Fatigue Quality List (FQL) [39]	X	X		
Cognitions with respect to activity	Tampa Scale for Kinesiophobia 2 (TSK2) [40]	X	X		
Affective quality of pain	McGill Pain Questionnaire (MPQ) [41]	X	X		
Causal attributions	CAL diabetes [42]	X	X		
Diabetes quality of life	Diabetes Quality of Life Brief Clinical Inventory (DQOL_BCI) [43]	X	X		
Cognitions regarding symptoms of chronic illness	Illness Cognition Questionnaire (ICQ) [44]	X	X		
	Cognitive and Behavioural Responses to Symptoms Questionnaire (CBRSQ) [45]	X	X		
Self-efficacy regarding diabetes self-care	Confidence in Diabetes Self-Care Scale (CIDS) [46]	X	X		
Physical activity	International Physical Activity Questionnaire (IPAQ) [47]	X	X		

T_0_ = baseline assessment; T_1_ = second assessment; T_2_ = post-treatment assessment for patients on the waiting list, T_3_ = follow-up assessment

### Assessments

The baseline assessment (T_0_) consists of two appointments at the ECCF. During both test sessions patients will complete questionnaires (Table 2). In the two weeks between the two sessions patients will wear an actometer to measure physical activity [27]. Patients will also record their symptoms and activities in a diary. In addition, blood glucose variability and HbA_1c_ will be assessed. After the baseline assessment patients will be randomised to either the Dia-Fit intervention group or the waiting list group. After five months the second assessment will be done (T_1_), consisting of the same measures as at baseline assessment. After T_1_ the waiting list group will start with Dia-Fit. The waiting list group will receive an extra assessment after therapy (T_2_). All patients will be assessed six months after finishing Dia-Fit (T_3_). T_2_ and T_3_ will consist of a limited number of measures (Table 2).

### Adverse events

Adverse events (AEs) will be assessed at T_1_. Patients will be asked to fill in a questionnaire regarding the development of new symptoms during the therapy or waiting period. All AEs that are spontaneously reported by patients or observed by the investigator will be recorded and reported to the ethical committee. The investigator will also record and report serious adverse events (SAEs) to the ethical committee. Previous research has shown that CBT for fatigue is a safe treatment [34].

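### The adverse event questionnaire is scheduled only at T1, so about half of the planned Dia-Fit courses have no solicited adverse event report for their treatment period

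*Protocol article*

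**What the plan says.** The Adverse events section of the protocol article names one time point and one solicited instrument: "Adverse events (AEs) will be assessed at T_1", followed by "Patients will be asked to fill in a questionnaire regarding the development of new symptoms during the therapy or waiting period". Unsolicited capture is described without a time limit: "All AEs that are spontaneously reported by patients or observed by the investigator will be recorded and reported to the ethical committee", and "The investigator will also record and report serious adverse events (SAEs) to the ethical committee".

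The Assessments section gives the order of events. T1 comes five months after randomisation. For the waiting-list group, treatment follows it: "After T_1_ the waiting list group will start with Dia-Fit". That group then has a further visit, T2, when its therapy ends, and all patients are seen at T3, six months after finishing. T2 and T3 carry a reduced set of measures. Table 2 marks CIS fatigue, SIP8 total, HbA1c and blood glucose variability at those visits. The SF36 pain subscale, the Pain Catastrophising Scale, the PAID and the BDI are marked at T0 and T1 only. Table 2 has no adverse event row at any visit.

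**The concern.** The questionnaire's window is the therapy period for the first arm and the waiting period for the second. Both halves of that window close at T1, so the waiting-list patients are asked about symptoms only for the months in which they received nothing. Once they are treated, their adverse events are known only if they mention them or someone notices them.

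What is at stake is the description of harms under Dia-Fit. The article presents this as the first trial of such an intervention in this population, so each treated patient is useful safety experience. The plan already uses the waiting-list courses for benefit: in Statistical analysis, the follow-up comparison takes post-treatment scores from T1 or T2 according to when the patient was treated. For adverse events, the same courses would be recorded by a different and usually less complete method. Any table of events in all treated patients would then mix solicited reports from one group with unsolicited reports from the other.

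**Working it through.** **Inputs.** From Sample size: difference 6, SD 8.6, power 0.90, two-sided alpha 0.05, drop-out 25 %, 60 per condition, 120 in total. From Randomisation: 1:1 allocation. From Adverse events and Assessments: questionnaire at T1; waiting-list treatment between T1 and T2.

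**The plan's own figure.** An exact two-sample t-test calculation gives 44.16 per arm, rounded up to 45. Inflating for drop-out, 45 / (1 − 0.25) = 60 per arm and 2 × 60 = 120. The stated numbers reproduce.

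**Share of courses without a solicited report.** Waiting-list courses divided by all courses:

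- As planned, no losses: 60 / (60 + 60) = 60/120 = 50 %.
- Assuming 25 % of the waiting-list arm leaves before starting Dia-Fit and the first arm is complete: 45 / (60 + 45) = 45/105 = 43 %.
- Assuming both arms lose 25 %: 45 / (45 + 45) = 45/90 = 50 %.

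The split of drop-out by arm and timing is not in the article, so 43 to 50 % is a range under assumptions. With the questionnaire also at T2, the planned coverage would be 120 of 120.

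**What the extra exposure would buy (illustration only).** For an event seen in none of n patients, the one-sided 95 % upper bound is 1 − 0.05^(1/n). The chance of seeing at least one case of an event with true rate p is 1 − (1 − p)^n.

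| Courses with solicited report | Upper bound, zero events | Chance of at least one case, p = 2 % |
|---|---|---|
| 60 | 4.9 % | 70 % |
| 120 | 2.5 % | 91 % |
| 45 (after 25 % loss) | 6.4 % | 60 % |
| 90 (after 25 % loss in both arms) | 3.3 % | 84 % |

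The 2 % rate is an assumption chosen for illustration; the article gives no expected adverse event rate.

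**What is measured at the end of treatment, by group.**

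| | First arm (T1) | Waiting-list arm (T2) |
|---|---|---|
| Questionnaire on new symptoms | yes | none stated |
| Spontaneous or observed AEs, SAEs | yes | yes |
| CIS fatigue, SIP8, HbA1c, glucose variability | yes | yes |
| Pain, diabetes distress, depression scales | yes | no |

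The gap is the first and last rows.

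**The case against.** A reader might infer that the waiting-list group has no systematic harm assessment under treatment. The article does not support that. Deterioration in fatigue, function or glucose control would show in the T2 measures, and spontaneous, observed and serious events are recorded with no stated cut-off. What is missing is the questionnaire, together with the scales not repeated at T2.

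A reader might also infer that worsening of existing complaints goes unmeasured, because the questionnaire asks only about new symptoms. At T1 this is largely answered by the repeated scales for fatigue, pain, diabetes distress and depression. It has force at T2, and there only for what is not repeated; fatigue is.

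Unequal therapist contact is a tempting argument against relying on spontaneous reports, but it does not apply here. Between T1 and T2 the waiting-list patients receive the same sessions and fortnightly e-mails that the first arm had. The imbalance in contact exists before T1, when both arms complete the questionnaire.

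It can further be said that the stated objective is efficacy, that the article plans no pooled harms analysis, and that data after T1 have no concurrent control. All of that stands. Post-T1 reports add exposure, not a comparison. The zero-event bounds are also a poor description of a symptom questionnaire in chronically fatigued patients, where zero counts are unlikely. The rare events for which such bounds matter are mostly serious, and those are recorded throughout.

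Finally, this is a condensed article. Table 2 omits adverse events even at T1, so its silence at T2 proves nothing, and the full protocol may schedule a later questionnaire. The point rests instead on the Adverse events section, which names T1 and no other time.

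**Conclusion.** The point holds in a limited form. As the article states the plan, solicited adverse event reports cover the treatment period of the first arm only, leaving 60 of 120 planned Dia-Fit courses (43 to 50 % under the drop-out assumptions shown) to unsolicited reporting plus the four outcome measures taken at T2. Ascertainment under treatment is therefore not the same in the two treated groups.

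It would be wrong to conclude that the trial's harm comparison is compromised. At T1 both arms answer the same questionnaire over the same five months, and that randomised comparison is intact, as is the primary analysis of CIS fatigue. The loss is in the completeness of the description of harms under Dia-Fit. This is a worthwhile, inexpensive improvement to a stated choice. The verdict assumes that no later questionnaire is scheduled in the full protocol.

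**What to change.** - Give the same adverse event questionnaire to the waiting-list group at T2, with T1 to T2 as its window, and add an adverse event row to Table 2.
- Preferably word it, for both arms at T1 and for the waiting-list arm at T2, to ask about new or worsened symptoms.
- Base the between-arm comparison of adverse events on the T1 questionnaire only.
- Report solicited events under treatment descriptively over the first arm (T1) and the waiting-list arm (T2), without a test. List spontaneous reports separately.

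The cost is an existing form at a visit already scheduled, a few minutes per patient and a minor amendment. Recruitment was still under way when the article was written. The drawback is that the data after T1 are uncontrolled and cannot separate effects of treatment from background symptoms; the report should say so. If the questionnaire is not added, the plan should state that solicited harms cover only the randomised period.

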### Intervention

Dia-Fit consists of blended care, a combination of assignments, information and e-mail contact delivered via an internet portal and individual face-to-face sessions with a therapist. The total duration of the intervention is five months. During these months patients get online information and assignments, have fortnightly e-mail contact with their therapist and receive five to eight face-to-face sessions. The intervention is aimed at changing cognitions and behaviours thought to maintain fatigue; these are depicted in Fig. 1. Which cognitions and behaviours are relevant and applicable for the individual patient will be determined on the basis of cut-off scores on various questionnaires filled in at baseline assessment and the clinical interview by the therapist. For each fatigue-perpetuating factor a treatment module is developed. In this way the intervention can be tailored based on the applicable factors. Patients can follow from three up to eight of the following modules:*Goals setting*. All patients receive this module. The module is the start of the Dia-Fit intervention and consists of psycho-education about fatigue in T1DM and the cognitive behavioural model of fatigue in T1DM. There will be a discussion about which modules are relevant for the patient. The patient will formulate goals of the therapy that, if attained, imply that a patient is no longer severely fatigued and no longer limited by fatigue in daily functioning.*Regulation of the sleep-wake pattern*. At baseline, patients register bedtimes, times that they get up and the time slept during the day for two consecutive weeks. This module is indicated if patients score 60 or higher on the subscale sleep of the Sickness Impact Profile 8 (SIP8) [23] and/or if their bedtime and get-up time registration shows evidence of a disrupted sleep-wake pattern. In this module the importance of a regular sleep-wake cycle is discussed. Patients are asked to maintain fixed bedtimes and get-up times and to stop sleeping or lying down during the day.*Formulating helpful fatigue-related beliefs*. This module addresses low self-efficacy with respect to fatigue, fatigue catastrophising and the tendency of patients to focus on fatigue. Dysfunctional beliefs will be reformulated and patients will practice applying helpful beliefs in their daily life. If patients score 19 or lower on the Self Efficacy Scale (SES) for fatigue [24] and/or 16 or higher on the Fatigue Catastrophising Scale (FCS) [25], they will receive this module. The tendency to focus on fatigue will be addressed if patients score 30 or higher on the Illness Management Questionnaire (IMQ) subscale focusing on symptoms [26]. Patients will learn how to shift their attention to other things instead of fatigue, such as activities or the environment. Patients will also be asked to stop talking about fatigue and to ask significant others to stop talking about fatigue.*Activity regulation and increasing the level of activity.* This module is applicable for all patients and focuses on gradually increasing activity. The physical activity pattern of patients will be assessed with an actometer at baseline. An actometer is a small device which is worn at the ankle during two consecutive weeks [27]. On the basis of the scores of the actometer, each patient will be categorised in one of the two activity patterns: relatively active or low active. The physical activity of relatively active patients varies from day to day and is often characterised by ‘all or nothing’ behaviour. Relatively active patients first learn to divide their activities more evenly across the day and week and then increase their physical activity with a graded activity program. Patients can choose to increase their physical activity level either by walking or biking. They start walking or biking at least two times a day and increase their walking or biking time step by step. Patients with a low active pattern immediately start by increasing their physical activity. After patients have increased their physical activity, they apply the same principles to social or mental activities. Only patients who experience specific problems with social or mental activities will receive these elements of the module. Patients who do not need this specific step and believe that they are able to increase their level of activity will proceed with other modules and the realisation of their goals.*Coping with pain*. This module focuses on dysfunctional cognitions regarding pain. It is assumed that catastrophising thoughts with respect to pain will make it difficult for patients to increase their activity level. Therefore, patients learn to use more helpful beliefs with respect to pain. Patients who score 55 or lower on the pain subscale of the SF36 [28] and/or 16 or higher on one of the two subscales, magnification and rumination, of the Pain Catastrophising Scale (PCS) [29] will receive this module.*Optimalisation of social support and interactions.* T1DM patients with severe fatigue can experience problems in their interactions with significant others due to a lack of understanding or support. In this module patients learn how to improve their communication with significant others about fatigue. In exercises they learn how to communicate with others about fatigue and how to be more assertive. There is also an emphasis on having more realistic expectations with respect to the reaction of others. This module is indicated if patients score 50 or higher on the subscale discrepancy and/or score 14 or higher on the subscale negative interactions of the Sonderen Social Support Inventory (SSI) [30].*Reducing diabetes-related distress*. T1DM is a chronic disease, and its management is demanding for patients. Patients can develop diabetes-related distress, for example, related to the fear of the development of medical complications, hypoglycaemia or deregulated blood glucose values. In this module patients concretise the elements of diabetes that they find stressful and learn how to better cope with these elements. The module is indicated if patients score 30 or higher on the Problem Areas in Diabetes (PAID) questionnaire [31].*Step-by-step realisation of goals*. All patients end Dia-Fit with the realisation of goals. Patients realise the preset goals and evaluate the treatment effects. Patients who work less because of their fatigue will resume work in this module. Therapists will discuss with patients how to prevent relapse.

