### Outcome measures

The primary outcome measure is fatigue severity measured with the fatigue severity subscale of the CIS [19]. The CIS subscale fatigue consists of eight items that are scored on a 7-point Likert scale from (1) ‘Yes, that is true’ to (7) ‘No, that is not true’. Scores range from 8 to 56 with higher scores indicating more severe fatigue. Severe fatigue is operationalised as scoring 35 and higher, which is higher than the mean plus two standard deviations of a healthy control group [32]. The CIS is a valid and reliable instrument that has been used before in patient groups with chronic diseases [12, 13].

Secondary outcome measures are limitations in daily functioning and diabetes control. Limitations in daily functioning will be measured with the total score on the Sickness Impact Profile 8 (SIP8) [23]. The SIP8 measures functional disability in eight different domains of functioning: sleep and rest, homemaking, mobility, social interactions, ambulation, leisure activities, alertness behaviour and work limitations. The eight subscale scores are added to provide one weighted score of disability (SIP8 total score). Higher scores indicate more disabilities. Diabetes control will be determined with two diabetes-specific clinical measurements: HbA_1c_ values and blood glucose variability. HbA_1c_ values are routinely assessed at the diabetes outpatient clinics every three months. Whenever possible, assessment of HbA_1c_ for the study and the routine assessment will be combined. Blood glucose variability will be derived from 7-point blood glucose profiles, measured for two consecutive days. The standard deviation of the mean glucose level is used as an indicator of blood glucose variability [33].

Questionnaires that will help decide which modules of the Dia-Fit intervention should be used are described in the section Intervention. Based on the model of fatigue in T1DM several fatigue- and diabetes-related cognitions and behaviours are assessed. Questionnaires and measurement points are listed in Table 2.

**Table 2 Tab2:** Time points of all measures

	Measurements	T_0_	T_1_	T_2_	T_3_

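### As described, the T1 adverse-event questionnaire is framed around new symptoms and no hypoglycaemia count sits beside HbA1c, so more frequent non-serious hypoglycaemia is not clearly solicited in either arm

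*Protocol article*

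**What the plan says.** The Adverse events section sets the timing of collection ("Adverse events (AEs) will be assessed at T_1") and the scope of the questionnaire ("Patients will be asked to fill in a questionnaire regarding the development of new symptoms during the therapy or waiting period"). Two further routes are open throughout: "All AEs that are spontaneously reported by patients or observed by the investigator will be recorded and reported to the ethical committee", and "The investigator will also record and report serious adverse events (SAEs) to the ethical committee".

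The Intervention section says of the activity module: "This module is applicable for all patients and focuses on gradually increasing activity". For the physical part it adds: "They start walking or biking at least two times a day and increase their walking or biking time step by step". Hypoglycaemia is named only in the distress module, as something patients may worry about: "related to the fear of the development of medical complications, hypoglycaemia or deregulated blood glucose values".

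Under Outcome measures, "Diabetes control will be determined with two diabetes-specific clinical measurements". These are HbA1c and glucose variability, the latter an SD from 7-point profiles on two consecutive days. Table 2 schedules both from T0 to T3 and lists no hypoglycaemia measure.

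**The concern.** Table 1 requires type 1 diabetes of at least one year's duration, and the Background says such patients inject insulin. For most of them a low glucose episode is a familiar event. Asked about symptoms that developed during the period, a patient whose episodes have become more frequent could truthfully report nothing new. Activity is increased in the treated arm before T1 and not in the waiting-list arm, so a difference in hypoglycaemia is plausible. The article gives no rate and does not say that one is expected.

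Two things are at stake. The first is safety ascertainment: a harm specific to insulin-treated patients may go uncounted, or be counted unevenly between arms. The second is the reading of a secondary outcome: a lower HbA1c can reflect better control or more time at low values, and the second glucose measure need not separate the two.

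**Working it through.** The plan gives no figure on this point, so the check sets the described routes of capture side by side and tests how far each would register more frequent non-serious hypoglycaemia.

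**1. Solicited questionnaire (T1, both arms).** Its described scope is new symptoms. An increase in an existing problem falls outside that description, though the form itself is not shown.

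**2. HbA1c and glucose SD (T0 to T3, both arms).**
- Readings per assessment: 7 × 2 = 14.
- Share of the period covered by the T1 profile, taking five months as about 150 days: 2 / 150 = 1.3%.
- Effect of a uniform shift: if every reading x becomes x − c, the mean falls by c but SD(x − c) = SD(x). HbA1c would be expected to fall, the SD would not change, and more readings could lie in the low range. The pair would then show lower HbA1c with unchanged variability, which does not distinguish better control from more lows.
- An SD also does not say whether the spread comes from high or low values.

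**3. Spontaneous and observed events.** These are not restricted to new symptoms, but the opportunity to report differs by arm. From the Intervention section:
- e-mail contacts: five months is about 21.7 weeks; 21.7 / 2 = 10.8, so 10 to 11;
- face-to-face sessions: 5 to 8;
- total before T1 in the Dia-Fit arm: 10 + 5 = 15 to 11 + 8 = 19.

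No trial contact is described for the waiting list between randomisation and T1. Routine three-monthly HbA1c checks at the outpatient clinics are mentioned under Outcome measures, but as usual care and not as a route for adverse-event reporting.

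**4. Serious adverse events.** A hypoglycaemic episode that qualifies as serious can enter here. A non-serious one does not.

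**5. Repeated scales and diary.** The Assessments section says T1 consists of the baseline measures. Fatigue, disability, pain, depression and diabetes distress are therefore measured again in both arms, so worsening in those areas is solicited even though it is not labelled an adverse event. The baseline symptom and activity diary may be repeated as well. Its content is not described, so whether it would record low glucose is unknown.

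**Result.** Of the five routes, none is described as counting non-serious hypoglycaemia in the same way in both arms.

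**The case against.** The strongest objection is that this is a condensed article. The questionnaire is summarised in one sentence, and its items may be broader than that sentence suggests. This stands: the point can only be made about collection as described. It does not remove the point, because the article states the questionnaire's scope and timing and the two glucose measures, and those stated choices leave the gap.

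A reader might infer three stronger things that the documents do not support.

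- **That worsening of existing symptoms goes uncaptured altogether.** It does not: fatigue, disability, pain and depression are re-measured at T1 in both arms, a diary may be repeated, and spontaneous and serious events are recorded.
- **That a fall in HbA1c will be presented as better control.** Nothing says so. HbA1c is paired with a second glucose measure, and both are analysed as two-arm comparisons with no directional claim. The ambiguity is a possible consequence, not a commitment of the plan.
- **That a between-arm adverse-event comparison is biased by contact frequency.** The Statistical analysis section plans no such comparison. Spontaneous events are recorded and reported to the ethical committee. Unequal contact would matter only if those reports were pooled into a comparison of arms.

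It is also fair to say that 1.3% of days and 15 to 19 contacts describe opportunity for observation. They do not measure missed events or bias.

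**Conclusion.** The concern holds in limited form. On the article's description, more frequent non-serious hypoglycaemia is not clearly solicited, the two diabetes-control measures would not reliably reveal it, and spontaneous reporting cannot stand in because the described opportunity is about 15 to 19 contacts in one arm and none in the other.

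The conclusion rests on three assumptions: that the questionnaire's items match its one-sentence description; that hypoglycaemia is generally an existing problem in this population; and that increased activity could plausibly change its frequency. The effect cannot be sized, because no hypoglycaemia rate is given. The point concerns safety ascertainment and the interpretation of one secondary outcome. The primary analysis and the sample size are untouched.

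**What to change.** 1. State how the T1 questionnaire is worded. If it matches the description, change it identically in both arms to ask about new or worsened symptoms, and add an item on hypoglycaemic episodes since T0.
2. From the 7-point profiles already collected, report the number of low readings by arm beside HbA1c and glucose SD, with the threshold fixed before the data are compared. With 14 readings per assessment this is descriptive only.
3. Interpret any HbA1c difference together with these two pieces of information.
4. If adverse events are compared between arms, base the comparison on the solicited questionnaire and list spontaneous reports separately.

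The cost is a few added items and one descriptive table. There are two drawbacks. Recall over five months is imprecise, although the question would be the same in both arms. Recruitment began in January 2014 and is ongoing, so patients already assessed at T1 will lack the new items, and the report should say how many. The low-reading count needs no new data and is available for every patient with profiles.
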